Finally, a detailed understanding of different organizational, individual, and intervention design factors that have the potential to alter intervention effects is needed [25, 26]. Tentative evidence suggests that CBT- and mindfulness-based interventions may be more effective for white-collar employees [14]. Organizational variables such as managerial support for recovery [35], a climate that supports segmentation between work and home [36] as well as the level of unfinished tasks [37] may also represent essential boundary conditions. In cases where the workplace does not favor psychological detachment from work, and the amount of work tasks does not permit it, intervention effects on detachment and well-being outcomes are likely to be attenuated. Considering individual factors, studies have discussed the role of treatment-by-baseline interactions in which individuals with different baseline levels of the variables of interest show different reactions to interventions [16]. Particularly those individuals who are more at risk with respect to well-being indicators have the potential to gain more from the intervention. Lastly, intervention design factors such as the length of the intervention, commitment to homework assignments, and training demands (i.e., the complexity of homework assignments) are likely to play a role in attenuating and accentuating CBT- and mindfulness-based intervention effects [14, 15].

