As CBT-based and MBSR interventions will most likely not be equally beneficial for all participants, we will further explore the moderating role of several organizational, individual, and intervention design factors. More precisely, we will focus on variables that have the potential to attenuate the effects of the intervention, primarily on psychological detachment and burnout (supervisor support for recovery, segmentation supplies, unfinished tasks, and time pressure). In line with previous studies, we will also consider compliance with intervention exercises, completion of homework assignments, and satisfaction with the interventions as potential moderating variables.

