#### Effect evaluation

The analyses will be carried out with SPSS [88] and Mplus [89]. The significance level used in the analyses will be .05. The main research questions (i.e., group differences in psychological detachment from work and burnout) will be analyzed with two separate two-way repeated measures analyses of variance (ANOVAs), with time as the within-subjects factor (3 levels: pre, post, follow-up) and group as the between-subjects factor (3 levels: CBT, MBSR, control), for each of the main outcomes separately. Significant interactions will be followed up with a simple effects’ analysis, using the Bonferroni correction to adjust for multiple testing.

The effects of the intervention on the secondary outcomes (i.e., general and work-related well-being) will be analyzed with a two-way repeated-measures MANOVA, with time as the within-subjects factor and group as the between-subjects factor. This analysis is contingent upon moderate correlations between the dependent variables [90]. Therefore, we will first examine correlations between the secondary outcome variables. Significant interaction effects will be followed-up with ANOVAs for each of the dependent variables and a discriminant descriptive analysis to further examine the effects. The moderation (i.e., supervisor support for recovery, work-home integration supplies, unfinished tasks, time pressure) and mediation (i.e., mindfulness, work-related maladaptive thinking patterns) effects will be analyzed using the PROCESS macro for SPSS [91]. T2 measures of the studied mediators will be utilized in these analyses. In order to explore both; the inter-individual variability and the intra-individual patterns of change trajectories in the mechanisms and the main outcomes during interventions, growth curve analyses will be conducted using data from the weekly questionnaires.

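### The protocol announces individual moderators and motivates baseline level as one, but the moderation analysis lists only four workplace factors, so that question goes untested and workplace moderation may be mixed with baseline severity

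*Protocol article*

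**What the plan says.** Three parts of the protocol article bear on this.

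- **Background.** On individual factors it says that "studies have discussed the role of treatment-by-baseline interactions in which individuals with different baseline levels of the variables of interest show different reactions". It adds: "Particularly those individuals who are more at risk with respect to well-being indicators have the potential to gain more from the intervention". On the organizational side, where the workplace does not favour detachment or the workload does not allow it, "intervention effects on detachment and well-being outcomes are likely to be attenuated".
- **Objectives and hypotheses.** Objective (e) is to explore boundary conditions. The text later says that "we will further explore the moderating role of several organizational, individual, and intervention design factors". It then names four workplace variables, "supervisor support for recovery, segmentation supplies, unfinished tasks, and time pressure", and three intervention design variables, "compliance with intervention exercises, completion of homework assignments, and satisfaction with the interventions as potential moderating variables". It names no individual variable.
- **Effect evaluation.** The moderation list reads "The moderation (i.e., supervisor support for recovery, work-home integration supplies, unfinished tasks, time pressure" and ends there. The method is the PROCESS macro. No model equation, covariate or measurement wave for the moderators is given; the only wave stated is T2, for the mediators.

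The Measures section puts burnout and detachment in the pre-screening, T1, T2 and T3 batteries, and the four workplace moderators in the T1, T2 and T3 batteries.

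**The concern.** Of the three announced classes of moderator, the analysis section carries one. The individual class has a rationale in the Background and data at T1, but neither a named variable nor an analysis. This is a mismatch between stated aim and stated analysis, not merely detail left for a fuller plan, because the analysis list is introduced as exhaustive.

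The gap may also affect how the workplace results are read. Time pressure, unfinished tasks and low supervisor support plausibly go with worse baseline burnout and detachment. The Strengths and limitations section itself treats organizational norms of constant availability and long hours as part of the cause of poor detachment. If people with worse baseline scores also gain more, a model with arm-by-workplace and no arm-by-baseline term can mix the two. A real attenuation in demanding workplaces could then be hidden, or a baseline effect could be reported as a workplace effect.

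**Working it through.** **1. Announced against analysed**

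| Class | Named in Background or Objectives | In the Effect evaluation list |
|---|---|---|
| Organizational | supervisor support, segmentation supplies, unfinished tasks, time pressure | all four (segmentation supplies appears there under an integration label) |
| Individual | baseline level (Background only) | none |
| Intervention design | compliance, homework, satisfaction | none |

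**2. The plan's own figure.** The only sample-size figure concerns the group-by-time test. For Pillai's trace with 3 groups and 3 times, df1 = 4, df2 = 2(N - 3) and noncentrality = 2 × N × .25². This gives power .9500 at N = 151 and .8005 at N = 98, so both stated figures reproduce. They do not bear on moderation, for which the protocol gives no figure.

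**3. Size of the possible mixing.** Let X be arm, W the workplace factor, B baseline severity and r = corr(B, W). B and W are standardised, and a higher outcome is better. If the true model contains g_w·XW + g_b·XB and the XB term is left out, the expected XW slope is

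g_w + r × g_b.

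The values of r, g_w and g_b are assumptions; the documents give none of them.

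- Opposing effects, g_w = -.30, g_b = +.30, r = .4: -.30 + .4 × .30 = **-.18**. For r = .3 to .5 the range is -.21 to -.15.
- Only baseline moderates, g_w = 0, g_b = .40, r = .4: 0 + .4 × .40 = **.16**, where the truth is 0.
- If r = 0 or g_b = 0, the shift is 0.

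**4. Simulated power and error rates.** Outcome = .5X - .5B - .1W + g_w·XW + g_b·XB + error (SD .8), two arms, two-sided .05, 6,000 runs per setting.

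| Setting | XW estimate without XB | Rejection without XB | Rejection with B and XB |
|---|---|---|---|
| 50 per arm, r = .4, -.30 and +.30 | -.18 | .16 to .17 | .37 |
| 33 per arm, same | -.18 | .13 | .25 to .27 |
| 50 per arm, r = .4, 0 and .40 | .16 | 15% | 5% |
| same, r = .3 | .12 | 10% | 5% |
| same, r = .5 | .20 | 20 to 21% | 5% |
| 50 per arm, r = .4, 0 and .20 | .08 | 7% | 5% |

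Ranges reflect differences between simulation runs. Adding B as a covariate without XB does not remove the shift: at 50 per arm and r = .4 the estimate stays at -.18 and false positives stay at 15 to 17%.

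**5. Effect of the entry criterion.** Participants must report at least moderate difficulties, which restricts the range of B. The protocol gives no cut-off, so take truncation at the median as an assumption. Then Var(B) = 1 - 2/π = .363 and Var(W) = 1 - .16 × (1 - .363) = .898. The slope of B on W is .4 × .363 / .898 = .162. The expected XW slope becomes -.30 + .162 × .30 = **-.25**. In simulation, power is .28 against about .37, and false positives are about 6% when only baseline moderates at .40.

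**The case against.** The strongest reply has four parts.

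- **Covariates are not described.** An article may leave PROCESS covariates to a fuller plan, and the Measures section groups these variables under moderators and control variables. So a reader may infer, but cannot establish, that the models omit baseline. What survives is narrower. Ordinary adjustment for T1 would not remove the shift, because only the arm-by-baseline term does. That term is itself a moderation effect, and the listed moderation effects do not contain it.
- **The baseline effect is not a hypothesis.** A reader might infer that the protocol expects baseline severity and workplace strain to act in opposite directions. The text does not go that far: at-risk individuals "have the potential to gain more from the intervention", and this is a Background remark. The objection stands in full.
- **Unadjusted workplace moderation is a legitimate quantity.** Arm-by-workplace without baseline describes in which workplaces the randomised effect is larger or smaller. Chronic time pressure may itself produce worse baseline burnout, so conditioning on baseline changes the question. A reader might infer that the workplace estimates are biased; the documents do not support that as a flat statement. This is why the extra term belongs in a sensitivity analysis.
- **The numbers are assumed.** They shrink under restricted range or a smaller baseline interaction, and even with the extra term power is only about .37. This also stands.

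It would also be too strong to say the individual question cannot be answered. The T1 data will exist; what is missing is a stated analysis.

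**Conclusion.** The concern holds in a limited form. The inconsistency is certain on the text: individual and intervention design moderators are announced, and the moderation list contains neither. The announced individual moderator therefore goes untested as the plan is written.

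The effect on the workplace estimates is conditional. It needs both a correlation between workplace factors and baseline severity and a non-zero baseline interaction. Both are plausible, but the protocol quantifies neither. Within the assumed values the consequence runs from nothing, through a modest shift under range restriction, to a loss of two fifths of the interaction (.12 of .30) and a false-positive rate about three times nominal (15% against 5%). Because moderation is exploratory, this affects the interpretation of objective (e) only.

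**What to change.** In Effect evaluation:

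1. Add the T1 level of the outcome as the pre-specified individual moderator, tested by arm-by-T1-outcome.
2. Include the T1 outcome as a covariate in the PROCESS moderation models.
3. State that the workplace moderators are taken at T1.
4. Report each workplace moderation model a second time with arm-by-T1-outcome added, as a sensitivity analysis, and comment where the workplace term changes materially.
5. State whether compliance, homework and satisfaction will be analysed, or remove them from the Objectives. They arise during or after the intervention, so they need a separate statement from the T1 moderators.

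The cost is small. Items 2 and 4 together add two terms in a two-arm contrast (T1 outcome and its product with arm), or three when all three arms are in one model. No new data are needed, and the planned sample size does not change.

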
In line with one of the main objectives, we will focus on (work-related) maladaptive thinking patterns and mindfulness as mechanisms of change behind both protocols. Maladaptive thinking patterns are inflexible, unreasonable, and negatively-valenced cognitions that may guide one’s attention toward work and may lead to excessive preoccupation with work-related tasks [40]. Within CBT, these maladaptive thinking patterns are labeled as negative automatic thoughts or cognitive distortions. Mindfulness, on the other hand, is defined as an aware and non-judgmental state of mind in which one’s attention is directed toward the present moment [14, 38, 42]. Given that CBT is primarily aimed at altering maladaptive thinking patterns and MBSR at increasing trait mindfulness, we assume mechanisms of change during our intervention will correspond to the main goal of each protocol. In other terms, we hypothesize that work-related maladaptive thinking patterns will act as a mechanism through which the CBT-based intervention will contribute to higher psychological detachment from work and improved well-being, and mindfulness will act as a mechanism of change for the MBSR intervention. Since the proposed mechanisms may not be intervention-specific [33, 34], we will also test whether maladaptive thinking patterns and mindfulness act as mechanisms of change in MBSR and CBT-based intervention, respectively. As authors have argued that the proposed mediators and outcomes should be monitored not only at the end but also during the intervention [27], we will measure work-related maladaptive thinking patterns, mindfulness, psychological detachment, and burnout levels also on multiple occasions during the intervention. We assume that we will be able to establish a timeline between the proposed mediators and outcomes with a decrease of maladaptive thinking patterns and an increase of mindfulness across the intervention weeks associated with the primary outcomes of interest.

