## Methods/design

### Study design

The randomized controlled trial will follow the recommendations of the CONSORT (Consolidated Standards of Reporting Trials) group, which is considered a gold standard in clinical practice regarding devising interventions as well as their reporting [43]. The study design is depicted in Fig. 1. The study will take place between October 2020 and February 2021. In order to reach the target sample size, the second round of data collection will take place between January 2021 and May 2021, and additional rounds of data collection will be carried out if needed. Data collection in both intervention groups (i.e., CBT- and MBSR protocol) and the control group will be carried out immediately before (T1) and after the intervention (T2). During the 6-week intervention period, weekly questionnaires will be sent out to participants. The follow-up data collection will take place 3 months after the end of the intervention (T3). During T1, T2 and T3, participants will be asked to fill out questionnaires addressing all studied constructs, whereas the weekly questionnaire will only encompass the central mechanisms and primary study outcomes (i.e., work-related maladaptive thinking patterns, mindfulness, psychological detachment, and burnout). During the intervention period, participants from both intervention groups will receive e-mail notifications every Monday and Thursday with information about the assignments and exercises. The initial e-mail will include instructions on how to access the online platform with CBT and MBSR exercises. The notification every Monday will remind participants to fill out the weekly questionnaire before they start with the new exercise. All exercises from previous weeks will be visible on the online platform. Upcoming exercises will not yet be available to ensure that participants will not skip the activities or perform them in random order. The online platform will automatically monitor whether the participants followed the instructions and performed the respective exercises. In case of non-compliance, reminders will be sent out the following day. After the intervention, participants from the waitlist control groups will receive access to the online platform and all intervention materials, which they can perform in any order. They will receive weekly e-mails reminding them to perform the exercises and encouraging them to practice them. After the intervention, each participant will have the opportunity to request individualized feedback on his or her results.

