### Participants and recruitment

The participants will be recruited from various organizations in Slovenia partnered with the leading institution and through different media channels. The intervention will also be advertised through university newsletters and webpages as well as a well-known Slovenian mental health platform. Interested participants will be able to apply for the study via an online form. Although we will not specifically exclude any professions, employees with knowledge-intensive jobs and high-stress occupations will be primarily targeted [44]. The recruitment stage will begin in August 2020. Following previous intervention studies in the workplace context (e.g., [17, 18]), participants will be pre-screened for eligibility. They will have to meet the following inclusion criteria: 1) being aged 18 or above, 2) working a minimum of 40 h per week and currently not on sick leave, 3) ability to commit (at least) 2 h per week to the online training, 4) ongoing internet connection and computer accessibility, 5) reporting difficulties with psychological detachment from work and burnout at least to a moderate extent. Participants undergoing other forms of treatment (psychotherapy, pharmacotherapy) or who have a clinical diagnosis of mental illness will not be eligible to participate. They will, however, receive additional information on relevant health care services and a link to mindfulness and CBT exercises they can practice on their own. Those eligible to participate will receive detailed information about the intervention and an online informed consent form. Participants who will commit to the study will be randomly assigned to one of the three groups. Following the approach by Querstret and colleagues [17], block randomization based on gender will be used. Participants will be randomized within blocks in such a way that an equal number of females and males are assigned to each of the groups because women exhibit more rumination and difficulties detaching from work at home (e.g., [17]). In order to control for expectations about potential benefits of the interventions, participants will be blinded to the intervention. Both the CBT-based and the MBSR intervention will be advertised as occupational stress-reduction interventions. The participants assigned to the waitlist control group will only be asked to participate in the study and fill out the questionnaires. They will also receive information regarding the delayed starting date of the training.

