### Potential mechanisms

#### Mindfulness

Based on a review of mindfulness measures [82], we decided to use The Mindfulness Attention and Awareness Scale (MAAS [83]). MAAS is comprised of 15 items that measure mindfulness as a trait and five items that measure mindfulness as a state. In our study, only the trait items will be used (e.g., “*I could be experiencing some emotion and not be conscious of it until some time later*”), which are answered on a 6-point scale ranging from 1 (almost always) to 6 (almost never). The Cronbach’s alpha in the validation study was .87 [83].

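### The mediation test fixes T2 mediator levels but states no T1 adjustment and no outcome wave, so it does not secure the mechanism-of-change and timeline claims

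*Protocol article*

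**What the plan says.** Objective (d) in Objectives and hypotheses is to find which mechanisms carry the intervention effects and whether they are general or intervention-specific. The same section expects temporal evidence from the weekly measurements: "We assume that we will be able to establish a timeline between the proposed mediators and outcomes".

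Effect evaluation sets out the analysis. Moderation and mediation "effects will be analyzed using the PROCESS macro for SPSS", and "T2 measures of the studied mediators will be utilized in these analyses". No covariate and no outcome wave is named. For the weekly data, "growth curve analyses will be conducted using data from the weekly questionnaires", with the stated purpose of exploring variability between people and patterns of change within them.

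Three other statements bear on this. At T1, T2 and T3, "participants will be asked to fill out questionnaires addressing all studied constructs" (Study design), so baseline mediators and outcomes will be available. For mindfulness, "only the trait items will be used" (Mindfulness section). On allocation, "Participants who will commit to the study will be randomly assigned to one of the three groups" (Participants and recruitment).

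**The concern.** Randomisation makes the groups comparable on the mediator, so the group-to-mediator path is protected. It does nothing for the mediator-to-outcome path. Within a group, people with lower trait mindfulness or more maladaptive thinking may also detach less and report more burnout, for reasons that were there before the trial. A T2 level carries all of that stable difference. If the programme also shifts the mediator, the product of the two paths can be significant although changing the mediator changes nothing.

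The programmes are built to move these mediators, so the problem arises when they work as intended. At stake is objective (d), and with it the article's stated hope of identifying the decisive ingredients. The weekly data could help, but a growth curve describes trajectories and does not by itself show which variable moved first.

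**Working it through.** The article gives no figure for mediation, so there is none to reproduce. Its sample sizes supply the arm sizes, and they do reproduce. For the 3×3 repeated-measures MANOVA interaction with f(V) = 0.25 and α = 0.05: df1 = 4, s = 2, λ = N × 2 × 0.0625, df2 = 2(N − 3). N = 151 gives λ = 18.875, df2 = 296 and power 0.950; N = 98 gives λ = 12.25, df2 = 190 and power 0.80. This gives about 50 or 33 per arm and has no other bearing here.

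**Inputs.** From the article: T2 mediator, randomised groups, 50 or 33 per arm, α = 0.05. Assumed, because the article gives none: 60% of the variance of each score is stable; the stable parts of mediator and outcome correlate 0.5; the programme shifts the mediator by a (in SD); the true mediator effect is b = 0. The comparison is one programme against control, with scores of unit variance within arm.

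**Expected coefficient for the mediator when b = 0.** Mediator at T1 and T2 correlate 0.6, as does the outcome across waves. Any mediator score and any outcome score correlate 0.6 × 0.5 = 0.30.
- No covariates: 0.30. At a = 0.5 the apparent indirect effect is 0.15 (simulated mean 0.153).
- T1 mediator added: (0.30 − 0.6 × 0.30)/(1 − 0.36) = 0.12/0.64 = 0.1875; indirect effect 0.094 (simulated 0.096).
- T1 mediator and T1 outcome added: with coefficient b for each mediator score and c for the T1 outcome, 1.6b + 0.3c = 0.30 and 0.6b + c = 0.60. Hence 1.42b = 0.12 and b = 0.0845; indirect effect 0.042 (simulated 0.043). It is not zero, because single T1 scores measure the stable parts with error.

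**Chance of a false significant result, hand check at 50 per arm and a = 0.5.** Without covariates: SE(a) = √(2/50) = 0.20, z = 2.5, chance 0.705; SE(b) = √(0.91/97) = 0.097, z = 3.10, chance 0.872; product 0.615. With a = 0 it is 0.05 × 0.872 = 0.044.

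With both T1 covariates:
- Residual variance of the T2 mediator: coefficients (0.6 − 0.09)/0.91 = 0.560 and (0.30 − 0.18)/0.91 = 0.132, so 1 − (0.6 × 0.560 + 0.3 × 0.132) = 0.624.
- Residual variance of the outcome: c = 0.549, so 1 − (2 × 0.0845 × 0.3 + 0.549 × 0.6) = 0.620.
- SE(a) = 0.20 × √0.624 = 0.158, z = 3.16, chance 0.886. SE(b) = √(0.620/(95 × 0.624)) = 0.102, z = 0.83, chance 0.131. Product 0.116.

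**Simulation** (1,500 runs per setting, 95% Monte Carlo interval for a × b, share of runs excluding zero):

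| Per arm | Shift a | No covariates | T1 mediator | T1 mediator and outcome |
|---|---|---|---|---|
| 50 | 0 | 5.1% | 1.7% | 0.5% |
| 50 | 0.3 | 25% | 13% | 6% |
| 50 | 0.5 | 58% | 31% | 12% |
| 50 | 0.8 | 85% | 35% | 14% |
| 33 | 0.5 | 33% | 16% | 6% |

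A separate simulation without covariates at 50 per arm gave about 4%, 24% and 63% for shifts of 0, 0.3 and 0.5. At a = 0.5 and 50 per arm, varying the stable correlation from 0.3 to 0.7 gives 28% to 68% without covariates and 7% to 24% with both.

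**Does the outcome wave matter?** At a = 0.5 and 50 per arm, without covariates, a T2 outcome gives 61% and a T3 outcome 62%; with both T1 covariates, 13% and 11%. Suppose mediator and outcome also share same-occasion variation (assumed r = 0.3). With both T1 covariates, a T2 outcome still gives 80% and a T3 outcome 27%. Baseline adjustment and temporal order therefore address different problems.

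**Timeline.** Set side by side, Objectives and hypotheses expects a time order between mediators and outcomes, while Effect evaluation names growth curves for exploring trajectories. No path from an earlier mediator to a later outcome is named.

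**The case against.** This is a condensed article, and covariates in PROCESS are a detail that an analysis plan often carries. A reader might infer that the plan rules out T1 adjustment. It does not: it is silent, and the T1 values will be collected. What stands is that the article does fix the mediator wave and stops there, so the test as written is not one of change.

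A reader might also infer that the mediation has no temporal order. The outcome wave is unstated, and a T2 mediator with a T3 outcome would be ordered. That defence is sound against the flat charge, but order alone leaves the false-positive rate where it was (61% against 62%).

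A third tempting reading is that stable differences will be reported as mechanisms, with both mediators looking active in both programmes. That needs each programme to move each mediator. The groups are randomised, and the rate stays near 5% where the mediator is not moved. The article allows for overlap between programmes but does not assert it, so the general-versus-specific question is weakened rather than made unanswerable.

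Finally, the timeline sentence is hedged, and growth curves of mechanism and outcome could be linked. Whether they will be is not stated.

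**Conclusion.** The concern holds in a limited form. The mediation test is specified with T2 mediator levels, without stated T1 adjustment or outcome wave, and the weekly analysis is not stated to test order. The claims about mechanisms of change and their timeline are therefore not secured.

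The size depends on how far a programme moves the mediator. At 50 per arm the false-positive rate is about 4–5% with no shift, 24–25% at 0.3 SD and 58–63% at 0.5 SD, the last falling to about 12% with both T1 covariates. At 33 per arm and 0.5 SD it is 32–33%, falling to about 6%. These rates rest on the assumed stable share and correlation; they show direction and order of size and are not properties of this trial. The trait wording of the mindfulness items makes a substantial stable share plausible but gives no figure for it.

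The change should be made because mechanisms are a main objective. The primary comparisons of detachment and burnout do not depend on it.

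**What to change.** 1. Enter the T1 mediator and the T1 outcome as covariates in every mediation model.
2. Name the outcome wave. Make T2 mediator with T3 outcome the ordered test, for CBT versus MBSR only: Study design gives the waitlist group the materials after the intervention, so its T3 values are not untreated.
3. Keep the T2-outcome contrasts against waitlist but describe them as association, since T1 adjustment does not remove same-occasion variation.
4. Add to the growth curves a lagged weekly model in Mplus: mediator at week t to outcome at week t + 1, adjusting for outcome at week t, with person-level intercepts.

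The cost is wording and somewhat more analysis; the measurements and the software are already planned. Fewer mediators will reach significance, and some bias remains after adjustment. The CBT-versus-MBSR test at T3 cannot detect a mechanism that both programmes move equally, so evidence on general mechanisms will rest on the T2 contrasts and the lagged weekly model. The plan should say so.
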